
**Figure 1 Fig1:**
[figure not shown]
**Planned flow of participants in the Promoting Aging Migrants’ Capabilities Study.**

The invitation process and data collection are conducted by trained research assistants and conducted in the language preferred by the participant. The standardised baseline assessment comprises an interview, measurements, and observation. Follow-up data, identical to the baseline assessment except for demographics, will be collected in both groups at 6- and 12 months after the intervention. The complete data collection form, as well as consent and participant information forms, can be retrieved by contacting the first author (SG) or last author ([name]). In addition, information on reasons for any non-adherence (e.g. discontinuation of intervention) and non-retention (i.e. consent withdrawn or lost to follow-up) will be collected. Data from municipal registers will also be obtained and used to study care consumption.

The recruitment of participants began in autumn 2012 and is planned to be completed by the end of December 2014. The intervention began at the same time as the inclusion, and will be completed no later than 6 months after the last inclusion. The 12-months follow-up will be completed in January 2016. A detailed study timeline is shown in Table 4.

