**Table 1 Tab1:** **Themes from the booklet used in senior meetings in the promoting aging migrants’ capabilities study**

**Themes from the booklet**	**Principal professional** *****
Aging	PT
Physical activity helps keep you physically fit	PT
Food is a prerequisite for health	PT
You can take care of problems with your health	RN
How to use medicines	RN
To cope with everyday life	OT
You do not need to feel insecure	OT
Technology in everyday life	OT
Will I lose my memory?	OT
Life events and quality of life during aging	SW
Anyone who needs help can get help	SW

*Physiotherapist (PT), registered nurse (RN), occupational therapist (OT), and social worker (SW).

The senior meetings are conducted by an operative group consisting of professionals employed in the urban district: an occupational therapist, a registered nurse, a physiotherapist, and a social worker. All professionals receive education and training on the programme content, and on leading groups prior to study commencement. The programme comprises four weekly senior meetings in small groups (four to six participants), in addition to an individual follow-up home visit two to three weeks after the last senior meeting. Having groups enables the possibility of peer education with participants learning from each other [39], and a person-centred approach increases the possibilities for participants to be seen as experts on their own situation [40]. Respect for the participant and his/her values and giving each participant the opportunity to maintain and develop his/her control over his/her own everyday activities, is essential in the meetings.

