Some minor but important adaptations of the original senior meetings protocol [24] were made when designing the Promoting Aging Migrants’ Capabilities Study. First, since several languages were to be involved, the study adopted a bilingual approach, where all written participant material is printed in Swedish and the participants’ mother tongue. Recordings of material to compact disc (CD) in participants’ preferred languages are also available. If needed and sought, interpreters are engaged in study activities. Second, based on the dialogue with the reference groups, a section covering how to handle post-traumatic stress in everyday life was added to the booklet. Third, when the booklet was revised, some smaller sections that were deemed redundant by personnel in the urban district were removed to reduce the text. Finally, to further clarify and consolidate the person-centred approach, seminars based on scientific literature and dialogue were held jointly with the operative group and research group.

In this intervention, the risk of causing adverse events is judged to be low. However, any unforeseen harm will be documented by the operative group and reported to both the research group and the steering committee. When necessary, adequate responsive actions, for instance referral to medical care, will also be taken. To promote comparability of RCT study groups, concomitant care and interventions during participation in the study will be avoided as much as possible. Participants randomised to the control group will not be included in the intervention, but will receive conventional care on their own initiative, as well as undergoing study baseline and follow-up assessments.

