#### Outcomes

Activities of daily living (ADL) is the primary outcome measure [42,43]. Secondary outcome measures are: physical frailty indicators (mobility, strength, balance, cognition, nutrition, fatigue, physical activity, and visual impairment), falls and fear of falls, symptoms, depression, healthcare consumption, self-rated health, life satisfaction, leisure activities, assistive technology, and social support. The outcomes have, to a large extent, been tested for validity and reliability. All outcome measures are to be assessed at baseline and at the 6- and 12-month follow-ups. Details are provided in Table 3.

**Table 3 Tab3:** **Outcome measurements and follow-ups in the RCT part of the promoting aging migrants’ capabilities study**

**Primary outcome**	**Measurement**	**T0**	**T1**	**T2**
		**baseline**	**6-months**	**12-months**
Activities of Daily Living (ADL)	The ADL-staircase	X	X	X
**Secondary outcome**	**Measurement**			
Fatigue	The Mob-T scale	X	X	X
Grip strength	North Coast-dynamometer	X	X	X
Physical activity	Questionnaire	X	X	X
	Physical and domestic activity scale	X	X	X
Balance	The Berg balance scale	X	X	X
Gait speed	Four-meter walking test	X	X	X
Weight loss	The Göteborg Quality of Life Instrument	X	X	X
Cognition	Mini Mental State Examination (MMSE)	X	X	X
Visual impairment	KM-visual acuity chart	X	X	X
Falls	Questionnaire	X	X	X
Fear of falls	Questionnaire	X	X	X
Symptoms	The Göteborg Quality of Life Instrument	X	X	X
Depression	GDS 20	X	X	X
Healthcare consumption	Register data	X	X	X
Self-rated health	SF 36 (one question)	X	X	X
Life satisfaction	Fugl-Meyer -LiSat	X	X	X
Participation/Leisure activities	Questionnaire	X	X	X
Assistive technology	Questionnaire	X	X	X
Social support	Questionnaire	X	X	X

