#### Recruitment, participant timeline, and randomisation

The results of the pilot study preceding this full-size RCT ([name], [name], [name]: Unpublished observations) indicated that the recruitment procedure described in the original protocol for the senior meetings [24] needed to be adjusted to be more effective. Therefore, a plan consisting of three waves of recruitment strategies was adopted. The waves are hierarchical and an appropriate wave was to be added if an antecedent wave was unsuccessful in reaching the target number for inclusion. The first wave implies that participants are drawn at random from official registers in the urban district. All addresses, equally divided between the populations (Finland and the four countries in the Balkan Peninsula), are listed in random order (two separate lists). Based on the sampling lists, participants will be consecutively included in the study until the decided sample size is reached (n≥65 from each population). Letters will be sent to all randomly selected persons asking them to participate in the study. Invited participants also receive a description of the study, how it is to be conducted, and what is expected of those consenting to participate. The letter stresses the fact that participation is voluntary; it is followed by a telephone call about 1–2 weeks later. If no telephone number is to be found in public records, a second letter with a request to make contact by telephone is sent. During the call, the persons will be informed verbally about the study and given the opportunity to ask questions if anything is unclear. They are also asked personally if they would like to participate, while again stressing that participation is voluntary. Everyone who fulfils the criteria for inclusion and decides to participate is randomised by the research assistant after baseline assessment to one of the two groups using sealed, opaque envelopes prepared by an unattached researcher. Participants living together in the same household are allocated to the same group. Wave two is identical to wave one but involves an expansion of the targeted area to also include another adjacent urban district with similar demographics. Finally, wave three entails word-of-mouth promotion through one-chain snowballing [44]. This strategy uses former study participants and key persons in the aforementioned reference groups to facilitate spreading information about the study. Interested persons fulfilling inclusion criteria are invited to contact the operative group for further information and to undergo baseline assessment when appropriate. The third wave also includes local radio station advertisements containing brief information in the participants’ mother tongue on the study and how to contact the operative group. A detailed overview of the planned flow of participants is provided in Figure 1.

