### Dissemination policy

Research articles with different focuses (e.g. the intervention outcome, the implementation output, and qualitative papers) will be submitted to relevant scientific journals. Individuals who fulfil authorship criteria should not remain hidden and should have authority over manuscript content. Similarly, those who do not fulfil such criteria should not be granted authorship. No professional writer will be employed in the writing of articles, but language validators will be engaged. The research findings are planned to be presented at appropriate national and international conferences. Information about results relevant to politicians, policy makers, and relevant personnel will be made at scheduled meetings. In addition, information for participants and the public will be given at public meetings in easily accessible premises in the targeted urban district, starting not later than 1 year after completion of the study. Popular science reports and summary research information in the participants’ mother tongue will also be compiled and made publically available.

For transparency, upon written request from recognized researchers in the field, the study’s lead researcher will consider sharing deidentified data. Such actions will be decided in line with the policy at the University of Gothenburg, and will be considered no later than 3 years after the collection of the 1-year post-randomisation interviews.

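### Follow-up in both arms is timed from the end of an intervention that controls never receive, while another section times it from randomisation, so the arms may be assessed at different times since baseline

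*Protocol article*

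**What the plan says.** Under Recruitment, participant timeline, and randomisation, the article states that follow-up data "will be collected in both groups at 6- and 12 months after the intervention". The same section says that each eligible person "is randomised by the research assistant after baseline assessment to one of the two groups", so baseline comes before allocation and before any programme contact.

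The Intervention section describes four weekly group meetings and "an individual follow-up home visit two to three weeks after the last senior meeting". It also says: "Participants randomised to the control group will not be included in the intervention". Controls have conventional care and the study assessments only.

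The Dissemination policy section, on data sharing, refers to "the collection of the 1-year post-randomisation interviews". The Outcomes section names no starting point: "All outcome measures are to be assessed at baseline and at the 6- and 12-month follow-ups".

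On dates, recruitment is to close at the end of December 2014, and the intervention "will be completed no later than 6 months after the last inclusion. The 12-months follow-up will be completed in January 2016". Table 4 lists the intervention up to 2014/Q3-Q4 but in no 2015 period, and lists no data collection in 2016.

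**The concern.** A visit schedule needs a start date that exists for every participant and is defined in the same way in both arms. The end of the intervention exists in one arm only. Someone scheduling control visits from this text must choose a date, and randomisation or baseline is an obvious choice. If the intervention arm is then scheduled from the end of its programme, it is assessed longer after baseline than the controls.

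This matters because the first hypothesis is that the programme prevents or delays deterioration, including dependence in ADL, which is the primary outcome. Participants must be independent in daily activities at entry. If decline accumulates with time, the arm assessed later shows more of it even when the programme has no effect. Change from baseline would then cover different intervals in the two arms. The assessors are not blinded, so nothing in the procedure rules out arm-specific scheduling.

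**Working it through.** **1. Anchors side by side**

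- Recruitment, participant timeline, and randomisation: after the intervention, both groups.
- Intervention: controls are not included in it, so they have no end date.
- Dissemination policy: one year after randomisation.
- Outcomes and Table 3: baseline, 6 and 12 months, with no anchor.

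One section names randomisation, one names the intervention, and none of the text shown gives controls a reference date.

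**2. The stated end date, January 2016**

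Inputs: last inclusion 31 December 2014; intervention ends at most 6 months later.

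- Clock from randomisation: 31 Dec 2014 + 12 months = 31 Dec 2015. This fits.
- Clock from the intervention, latest permitted end: 31 Dec 2014 + 6 + 12 months = 30 June 2016. This does not fit, and Table 4 has no data collection then.
- Clock from the intervention, first meeting on the last inclusion day: 31 Dec 2014 + 5-6 weeks + 12 months = 4-11 February 2016. This is just outside.
- Reversed: for 12 months after the intervention to end by 31 Jan 2016, the last programme must end by 31 Jan 2015. Subtracting 5-6 weeks, its first meeting must be held by about 20-27 December 2014, before recruitment closes.

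**3. Possible lag between arms**

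Assumption: controls are timed from randomisation, and the intervention arm from the end of its programme.

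- Minimum: four weekly meetings span 3 weeks; adding 2-3 weeks to the home visit gives 5-6 weeks, or 1.15-1.38 months (days / 30.44). The 6-month visit (T1) falls at about 7.1-7.4 months since randomisation and the 12-month visit (T2) at 13.1-13.4.
- Any wait for a group of four to six to fill is added to this.
- Outer limit for the last inclusions: 6 months, so T1 at 12 and T2 at 18 months.
- If controls are given a matched date: about zero.

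**4. Illustrative effect on the comparison**

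Assumptions, none of them in the article: ADL decline treated as a yes/no event, constant hazard, 20% decline at 12 months, no true effect.

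h = -ln(1 - 0.20)/12 = 0.0186 per month; risk at lag L months = 1 - exp(-h(12 + L)).

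| Lag | Intervention arm | Control arm |
|---|---|---|
| 5 weeks (1.15 months) | 21.7% | 20% |
| 6 weeks (1.38 months) | 22.0% | 20% |
| 3 months | 24.3% | 20% |

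The 3-month row stands for programme length plus a wait for the group. The article gives no figure for that wait.

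**The case against.** The strongest reply is that the article gives one schedule for both groups, which is compatible with each control getting a reference date matched to the intervention arm. The timing gap could then be close to zero. The planned participant flow is in Figure 1, which is not shown, and a condensed article may leave visit scheduling to a fuller document. This stands in part: a reader might infer that the arms *are* assessed at different times, but the article does not say so. It does not remove the conflict between the two stated anchors, and if matching is intended, the text shown does not say it.

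A reader might also take January 2016 as proof that the true clock is randomisation. It is not. Table 4 shows no intervention in 2015, and a programme ending by January 2015 plus 12 months also reaches January 2016. The 6-month allowance is an outer limit, not the expected course. So the dates show that the stated rules are inconsistent; they do not show which clock is meant, nor that late participants will lose their 12-month visit.

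Larger losses can be calculated by applying lags of 4-6 months to the whole intervention arm, but the article supports 6 months only as a ceiling after the last inclusion. The 20% rate and the yes/no endpoint are assumptions too; the article plans non-parametric methods for ordinal data. Finally, the bias would run against the programme, so it would not create a false claim of benefit.

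**Conclusion.** The point holds as a defect in how the follow-up clock is fixed. The stated rule has no meaning for controls, it conflicts with the one section that names an anchor, and at its permitted limit it overruns the stated end of follow-up by about five months (June against January 2016).

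Unequal timing between arms is a risk, not a stated fact. If it occurs, the lag is at least 5-6 weeks, longer where groups take time to fill, and at most 6 months for the last inclusions. At the minimum lag the spurious difference is small, about 2 percentage points under the assumed 20% decline; at 3 months it is about 4. Both figures depend on controls being timed from randomisation and on the assumed constant hazard. The direction, against the intervention, requires only that ADL dependence increases with time. The planned sample size is unaffected.

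**What to change.** State that T1 and T2 fall 6 and 12 months after randomisation for every participant, with the same visit window in both arms. Bring the Recruitment, participant timeline, and randomisation section, Table 4 and the Dissemination policy section into line with this, and reconcile the 6-month allowance for completing the intervention with Table 4, which shows none in 2015.

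For participants already assessed, record the actual time since randomisation and report its distribution by arm. If the arms differ, add a sensitivity analysis, for example one restricted to visits within a common window. Simply adding elapsed time as a covariate is a weak remedy, because arm would partly determine it.

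The cost is wording and scheduling. The one downside is that the intervention arm's visits fall somewhat sooner after its programme ends.

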**Table 4 Tab4:** **Promoting aging migrants’ capabilities study timeline**

**Period:**	**2009-2012**	**2012/Q1 – Q2**	**2012/Q3 – Q4**	**2013/Q1 – Q2**	**2013/Q3 – Q4**
**Activities:**	Establish contacts	Formation of research organisation	Training of personnel	Recruitment of participants	Recruitment of participants
	Pre-planning	Establishing study protocol	Recruitment of participants	Intervention	Intervention
	Formation of steering		Intervention	Data collection	Data collection
	committee		Data collection	Pilot study	Pilot study publication
**Period**	**2014/Q1 – Q2**	**2014/Q3 – Q4**	**2015/Q1 – Q2**	**2015/Q3 – Q4**	**2016/Q1 – Q2**
**Activities:**	Recruitment of participants	Recruitment of participants	Data collection	Data collection	Article writing
	Intervention	Intervention	Data analyses	Data analyses	Dissemination of results
	Data collection	Data collection	Article writing	Article writing	
	Study protocol publication	Data analyses		Reporting to funding agencies	
		Article writing			

#### Masking (blinding)

Because of the nature of the intervention, neither participants nor the professionals in the urban district can be blinded to allocation in the RCT. In addition, supported by the pilot study results, assessors cannot be blinded since we need to match assessors and participants linguistically. Finally, we also assume that there would be less attrition if the participants could meet the same assessor at most of the follow-ups.

#### Power calculation

The power calculation was based on results gained in the preceding study ‘Elderly Persons in the Risk Zone’ [24], using the Berg balance scale as a basis. The Berg balance scale is one of the secondary outcome variables (range 0–56), with assumed mean values for the intervention and control groups of 32 and 28, respectively (15% difference), and a standard deviation of 8 in both groups. To be able to detect a significant difference between the two groups in a two-sided test with a significance level of 0.05 and 80% power, we need at least 65 persons in each group. Therefore, a total of at least 130 persons will be included.

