## Methods/Design

The Promoting Aging Migrants’ Capabilities Study has a descriptive, analytical, and experimental design. It is both an RCT and an implementation study, containing the collection and analysis of both qualitative and quantitative data. The combination of quantitative and qualitative methods in the study will best answer the research questions, as well as taking advantage of the strengths of both methodological approaches [35]. The participants in the RCT are randomised into two study arms (one intervention and one control group), and outcomes at 6- and 12-month follow-ups will be analysed. A pilot study has been conducted before the full-scale RCT to assess the feasibility of the programme, and has guided the final protocol ([name], [name], [name]: Unpublished observations). The implementation part of the study has a case study design [36], and will be carried out alongside the RCT. In addition, individual in-depth interviews of both participants and personnel will be conducted to determine the perceived effect and significance of the programme.

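### The 65 per group needed at analysis for the Berg balance scale is also the number enrolled, so the stated 80% power holds only if loss to follow-up is about 2% or less

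*Protocol article*

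**What the plan says.** The Power calculation section uses the Berg balance scale, which it identifies as a secondary outcome. It takes "assumed mean values for the intervention and control groups of 32 and 28, respectively (15% difference") and "a standard deviation of 8 in both groups", "in a two-sided test with a significance level of 0.05 and 80% power". From these it concludes: "we need at least 65 persons in each group. Therefore, a total of at least 130 persons will be included".

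The same total governs enrolment elsewhere. Table 2 gives 130 as the target sample size. The Recruitment section says "participants will be consecutively included in the study until the decided sample size is reached (n≥65 from each population"), which counts 65 per country-of-birth population rather than per arm but leaves the total at 130. The Data management section treats the target as fixed when it explains why no monitoring committee is needed.

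Losses are expected. The Masking section gives as a reason for unblinded assessors that "we also assume that there would be less attrition if the participants could meet the same assessor at most of the follow-ups". The text after Figure 1 says that information on reasons for "non-retention (i.e. consent withdrawn or lost to follow-up) will be collected". The Statistical analyses section discusses imputation, leaves the method open, and promises a comparison with complete cases. Outcomes are analysed at 6 and 12 months. No section gives an attrition rate or inflates the sample size.

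**The concern.** A sample-size formula gives the number of participants whose outcome must be observed. The article uses that number directly as the number to enrol. Participants are 70 or older and are followed for up to a year, and the protocol plans for withdrawal and missing values, so some randomised participants will probably have no follow-up Berg score. The power actually available is then below the figure stated.

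This is the only power figure in the article. A reader of a null Berg result would assume 80% power for a 4-point difference, when on the protocol's own assumptions the power may be several points lower.

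**Working it through.** **Inputs (Power calculation section).** Difference 32 − 28 = 4 points; SD 8; standardised effect 4/8 = 0.5; two-sided α = 0.05; power 80%; two arms, taken as equal in size from the 65 per group.

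**Step 1: reproduce the stated figure.**
- Normal approximation: n = 2 × (1.960 + 0.842)² × (8/4)² = 62.8, so 63 per group.
- Two-sample t-test (noncentral t): 63.8, so 64 per group.

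The stated 65 is consistent with this, and power at 65 analysed per group is 80.8% by t-test. The margin over the t-test requirement is 65 − 64 = 1 person per group, or about 1.5%.

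**Step 2: is there room for an allowance?** The section goes from 65 needed per group to 2 × 65 = 130 included, with no step between. Sixty-five is therefore both the evaluable number and the enrolled number.

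**Step 3: power when some of the 65 are lost.** The documents give no attrition rate, so the rates below are assumptions. Analysed per group = 65 × (1 − loss). Power is from the noncentral t with effect 0.5. The last column is the difference detectable with 80% power at SD 8.

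| Assumed loss | Analysed per group | Power for 4 points | Detectable difference |
|---|---|---|---|
| 0% | 65.0 | 80.8% | 3.96 |
| 2% | 63.7 | 79.96% | 4.00 |
| 5% | 61.8 | 78.7% | 4.07 |
| 10% | 58.5 | 76.5% | 4.18 |
| 15% | 55.3 | 74.0% | 4.30 |
| 20% | 52.0 | 71.4% | 4.44 |
| 30% | 45.5 | 65.5% | 4.75 |

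Power reaches 80% at about 2% loss and falls below it beyond that.

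**Step 4: rank test.** The Statistical analyses section prescribes non-parametric methods for ordinal data. If the Berg score is treated as ordinal (an assumption), and the rank test has efficiency 0.955 relative to the t-test under normality, the requirement is 64/0.955 = 67.0, or about 67 per group. Power with 65 enrolled is then about 78.9% with no loss, 74.5% at 10% and 69.4% at 20%.

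**Step 5: baseline adjustment.** Adjusting for the baseline Berg score changes the effect to 0.5/√(1 − ρ²), where ρ is the correlation between baseline and follow-up. The documents give no ρ. At 20% loss (52 per group):
- ρ = 0.3: effect 0.524, power about 75%.
- ρ = 0.5: effect 0.577, power about 83%.

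Recovery of 80% therefore depends on an unknown correlation and on an analysis to which the protocol does not commit.

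**The case against.** **The arithmetic is right.** This stands. The inputs give the output, and nobody should infer that 65 is miscalculated. The fault is that the result is used as the enrolment number.

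**An article may leave a dropout allowance to the full protocol.** This has limited force. The article states both the number needed and the number included and derives one directly from the other, which leaves no place for an allowance made elsewhere.

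**The total is worded as a minimum.** That would permit over-enrolment, but no margin is planned. Table 2, the Recruitment section and the Data management section treat 130 as the target and stopping point.

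**Intention-to-treat with imputation keeps 130 in the analysis.** Keeping 130 rows does not bring back unobserved outcomes, and the complete-case comparison will have the reduced numbers. It would be too strong to say that imputation adds nothing: a method based on a participant's own baseline uses some relevant information. It does not restore full power.

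**Baseline adjustment could offset the loss.** It could, as the working shows. But the Statistical analyses section adjusts only where baseline differences make it necessary, and the power calculation does not use adjustment.

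**The loss may be small.** This also stands. At 5% loss, power is about 2 points below the no-loss 80.8% and about 1 point below the stated 80%. The figures near 70% need an assumed loss of 20% or more.

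**Conclusion.** The point holds in a conditional form. The stated 80% power for a 4-point Berg difference is met only if loss is about 2% or less. Over an assumed 10 to 20% loss, unadjusted t-test power is about 76% down to 71%, and it is 65.5% at 30%. These figures rest on the protocol's own means and SD, equal arms, equal loss in both arms and independent observations. Couples and other household members are allocated together, which the figures ignore.

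Two stronger readings are tempting and are not supported:
- *That the trial fails to deliver 80% power at 12 months.* The documents give no attrition rate, and the power calculation names no time point, so this cannot be stated as fact.
- *That a null result on the primary outcome would be misread as coming from an 80%-powered trial because of attrition.* The 80% never applied to the primary outcome. It refers to the Berg scale, and no power is stated for ADL with or without losses.

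The matter should be corrected, but it concerns how power is stated and does not invalidate the design.

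**What to change.** Keep 130 and rewrite the Power calculation paragraph to say that:
- 65 per group is the number required with an observed outcome (64 by t-test).
- The power refers to the Berg balance scale only and not to the primary ADL outcome.
- No attrition rate is available, and 130 randomised gives about 76% power at 10% loss and 71% at 20% for a 4-point difference or, equivalently, 80% power for about 4.2 to 4.4 points.
- These figures are for an unadjusted t-test and are somewhat lower if a rank test is used.

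Do not claim that baseline adjustment recovers the loss unless adjustment for the baseline Berg score is prespecified and a range of correlations is shown (at 20% loss, about 75% power at correlation 0.3 and 83% at 0.5).

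The cost is one paragraph and a less favourable stated power. No extra participants and no change in conduct are needed.
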